### Outcomes and measures

An overview of all outcome measures and the different assessment moments in which they will be used is shown in Table 1.

**Table 1 Tab1:** Schedule of Enrolment, Interventions, and Assessment

		Study Period			
	Enrolment	Allocation		Post-allocation	
TIMEPOINT	Screening	Baseline	3 months	Post-treatment	Follow- up
**ENROLMENT**					
**Eligibility screen**	x				
**Informed consent**	x				
**Allocation**		x			
**INTERVENTIONS:**					
***SIDAS***	x	x		x	x
***LPC***	x	x		x	x
***AQ-Short***	x				
***BDI-II***		x		x	x
***Demographics***		x			
***DERS***		x	x	x	x
***EQ-5D***		x		x	x
***MANSA***		x		x	x
***PSP***		x		x	x
***SIAS***		x		x	x
***SRS-A***		x		x	x
***TAS-20***		x		x	x
***TIC-P short***		x		x	x
***WAV-12***^***a***^		x	x	x	x

*SIDAS* Suicidal Ideation Attributes Scale, *LPC* Life time Parasuicide Count, *AQ Short* Autism spectrum quotient (short), *BDI-II* Beck Depression Inventory – Second Edition, *DERS* Difficulties in Emotion Regulation, *EQ-5D* EuroQol 5 dimensions, *MANSA* Manchester short Assessment of quality of life, *PSP* Personal and Social Performance Scale, *SIAS* Social Interaction Anxiety Scale, *SRS-A* The Social Responsiveness Scale, *TAS* Toronto Alexithymia Scale, *TiC-P short* Trimbos/iMTA questionnaire for Costs associated with Psychiatric illness, *WAV-12* Working Alliance Inventory

^a^will be rated by participants and individual therapists after each completed session of the skills training module

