### Other secondary objectives

In the current study we will conduct additional research to explore the mechanisms of change related to the treatment outcome variables. It is hypothesised that both emotion regulation and therapeutic alliance mediate the effects of therapy. The level of alexithymia is hypothesised to moderate the effects of therapy.

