## Methods/design

### Design

This study is a single-blind multicentre randomised controlled trial with two arms: dialectical behavioural therapy (DBT) versus treatment as usual (TAU). TAU consists of weekly sessions of 30–45 min with a psychotherapist or social worker. The two groups will be compared at baseline, post-treatment (6 months), and at follow-up (12 months). The mediators will also be assessed mid-treatment at 3 months. All analyses will be performed according to the intention-to-treat principle. This trial meets all the requirements of the SPIRIT Protocol Checklist which provides guidance for protocols of clinical trials [41]. Checklist is provided in Additional file 1.

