### Study interventions

The therapy consists of DBT skills training [46], individual cognitive behavioural therapy [47], and weekly meetings with the consultation team for all trainers and therapists for 1 h. The complete staff will be supervised once a month by a fully certified trainer and supervisor ([name]).

Two adaptations were made to the standard DBT program for this study protocol. First, the telephone consultation (if needed) was limited to the therapist’s availability, which means that not all patients could use 24-h consultation. Second, the treatment period is limited to half of the original treatment time (1 year) because of the expected reduced concentration span. The preference for repetitive instructions in people with ASD, in combination with the concentration span, led to the decision to offer the skills training twice a week [48].

Individual cognitive behavioural therapy will take place on a weekly basis. The order and topics of each session are pre-determined based on Linehan’s hierarchy [15, 16]: suicidal and self-destructive behaviour, therapy interfering behaviour, quality of life interfering behaviour, and generalisation of the skills taught in the training. Each therapy session starts with self-report diary cards [49] that describe problematic behaviours and behaviours that influence the primary goals such as alcohol and drug use, the urge to self-harm, substance abuse, dissociation, level of applied skills, etc. Two skills training groups will take place each week. The skills taught are self-regulation skills, change skills, self-acceptance and acceptance of others, mindfulness, interpersonal effectiveness, and skills to cope with crises. When a meeting is missed, the participant will be asked to catch up by watching video recordings that are made of all the trainings sessions. The therapists keep track of self-reported watching by the experimental subjects. We consider that being in the programme for 5 months is the minimum number of sessions required for an adequate amount of intervention. All therapists are either psychologists or psychiatrists and skill trainers are psychologists, registered nurses, or social workers (*n* = 28). They will have 5 days of training in DBT by a licensed DBT therapist, teacher, supervisor, and trainer (AH).

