The control group will receive treatment as usual. This can be any form of treatment for suicidality in autism which is common within mental health care and is delivered in weekly sessions of 30–45 min with a psychotherapist or social worker. Therapists will only participate in one of the conditions.

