### Data analysis

The result of randomization will be checked by comparing baseline sociodemographic and clinical parameters between DBT and TAU condition, using univariate analyses. The study is intention-to-treat. So, all patients that have been randomized, will be in the analysis. If patients miss measurements, this will be dealt with LMM that uses expectancy maximisation to impute missing data. If patients miss four sessions in a row, the patient is considered a treatment dropout and therapists will stop pursuing the patients to continue treatment. Treatment drop-out will still be contacted for measurements, though. Treatment dropouts will still be part of the analysis in the intention-to-treat analysis. Study dropouts that have missing measurements will have the LMM imputation strategy to estimate scores and impute these bases on expectancy maximisation. If *p*-values are marginally, we will also use LOCF, last observations carried forward, as an imputation strategy to do a conservative sensitivity analysis. The primary outcome on the suicidality measures will be analysed using Linear Mixed Models (LMM) where condition is the fixed effect, measurement moment and site is a fixed factor, individual is a random effect with the baseline value as a covariate. The group x moment interaction will be assessed for post-treatment and follow-up results. We are aware that the SIDAS is used both in selection of patients and as an outcome measure and that regression to the mean may negatively impact on the interaction effect. The SIDAS score will probably not regress to normal score levels and cause a bottom effect. To cope with the regression to the mean, we compute the main effects of condition and time and the interaction of condition x time with baseline as a covariate. To identify mechanisms of change and the strength of the factors involved, both multilevel models and structural equation models will be used for mediation analyses. Mediation analysis with a multiple mediator model (multiple mediators in the same model) will be calculated with 5000 bootstraps using the PROCESS macro published by Hayes and Rockwood (2017) [58]. Moderators will be analysed using mixed modelling, in addition to the effectiveness analysis. Cost-utility analysis will also be performed.

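### The WAV-12 footnote ties alliance ratings to sessions that only DBT patients attend and conflicts with its own table row, so alliance measurement in TAU is undefined for the planned mediation analysis

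*Protocol article*

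**What the plan says.** Under Other secondary objectives the protocol article names two mechanisms of change: "It is hypothesised that both emotion regulation and therapeutic alliance mediate the effects of therapy". Under Data analysis, both go into one model: "Mediation analysis with a multiple mediator model (multiple mediators in the same model) will be calculated with 5000 bootstraps".

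Two instructions cover when alliance is measured.

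- **Footnote a to Table 1**, attached to the WAV-12 row label, says the scale is "rated by participants and individual therapists after each completed session of the skills training module".
- **The WAV-12 row of Table 1** marks baseline, 3 months, post-treatment and follow-up. No mark is limited to one arm. The Design section adds: "The mediators will also be assessed mid-treatment at 3 months".

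On who attends skills training, Study interventions says: "The therapy consists of DBT skills training [46], individual cognitive behavioural therapy [47], and weekly meetings with the consultation team". It then gives the frequency: "Two skills training groups will take place each week". For the other arm it says "The control group will receive treatment as usual", described as one short individual session a week. No skills-training module is mentioned for TAU.

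**The concern.** The footnote is the only text that says who completes the WAV-12 and on what occasion. That occasion does not exist in TAU, and no TAU equivalent is given. A mediation analysis of DBT versus TAU starts from the effect of arm on the mediator, so it needs alliance measured in both arms and in a comparable way.

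The footnote also does not fit its own row. At baseline no trial session has taken place, because baseline data precede allocation. At follow-up the six-month programme has ended.

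At stake is one of the two named mechanisms. An analysis plan written later cannot repair this, because it cannot recover ratings that were never collected.

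**Working it through.** The article gives no figure for this point. The arm size used below comes from the Sample size section and reproduces: effect size 0.50, power 0.80 and alpha 0.05 (two-sided assumed) give 63.77 per arm from the two-sample t-test. Rounded up, that is 64 per arm and 128 in total, with power 0.801.

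**Inputs**

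- 64 per arm (Sample size).
- Two skills-training sessions a week for 6 months (Study interventions, Abstract), taken as 26 weeks. The 26 weeks is an assumption.
- Four WAV-12 visits, three of them after allocation (Table 1).

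**First mediation path.** Alliance = i + a × arm, with arm = 1 for DBT and 0 for TAU. The coefficient a can be estimated only if the intercept and arm columns are linearly independent among participants with a WAV-12 score.

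*Reading 1: the footnote governs.* 64 DBT and 0 TAU participants have scores. Both columns are all ones, so the rank is 1 of 2. The cross-product matrix has rows (64, 64) and (64, 64), and its determinant is 64 × 64 − 64 × 64 = 0. Only the sum i + a can be estimated. The mixed-model handling of missing measurements in Data analysis does not help, because an arm with no observed values carries no information on its own mean.

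*Reading 2: the visits govern in both arms.* 64 + 64 participants are due a score. The matrix has rows (128, 64) and (64, 64), and its determinant is 128 × 64 − 64 × 64 = 4096. The rank is 2 of 2 and a is estimable. The footnote is then wrong, and the baseline cell still does not say which working relationship is being rated.

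*Reading 3: both apply.* A DBT participant gives up to 2 × 26 = 52 session-linked ratings plus the visit ratings. A TAU participant gives the visit ratings only. The path can be computed, but alliance differs between arms in the number of ratings and in their timing relative to therapy contact. If session ratings enter the DBT score, a mixes a difference in alliance with a difference in measurement.

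The 52 is a ceiling that assumes full attendance.

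**The case against.** The strongest reply is that the article does schedule the WAV-12 in TAU. The row has the same visit pattern as the DERS, the other mediator. The 3-month mediator assessment is not limited to DBT. Recruitment and study procedures places the 6-month assessment, and the 12-month measurement of all secondary outcomes, in both conditions, and the WAV-12 is listed under Secondary outcomes. It is a general client–therapist scale that TAU patients and their therapists could complete. All of this stands, and it limits the point in three ways.

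- **Alliance mediation impossible.** A reader might infer that 0 of 64 TAU participants will have data and that the alliance path cannot be estimated. The documents do not support this as a flat statement. It holds only if the footnote overrides its own row.
- **Emotion-regulation path lost too.** A reader might infer that TAU would also drop out of the DERS path, since both mediators share a model. That needs no TAU alliance data at all and also complete-case handling. Data analysis does not state complete-case handling for the mediation model, and it names multilevel and structural equation models besides the PROCESS macro.
- **Therapists rating sessions led by others.** A reader might infer that individual therapists must score sessions that skills trainers lead. The footnote sets when the rating is made. What is rated, according to the WAV-12 description, is the working relationship.

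It can also be said that mediation is exploratory here, and that an article may leave the logistics of TAU ratings to the full protocol. The first part bears on severity. The second does not remove the point, because the article states a collection rule, and that rule conflicts with its own table.

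**Conclusion.** The point holds as an internal contradiction that leaves the TAU alliance measurement undefined. Depending on which instruction the sites follow, the arm-to-alliance path is not identified (0 of 64 TAU participants with scores), is estimable with a wrong footnote, or rests on scores collected differently in the two arms. The text needs correction under each of these readings.

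This rests on skills training being given only in DBT, as the article describes it, and on the row marks applying to both arms, which the article implies but does not say in the table. The sample size and the primary comparison are untouched. The correction should be made because one of the two hypothesised mediators depends on it, but it does not threaten the trial's main result.

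**What to change.** Rewrite footnote a so that, in both arms, the patient and the individual therapist rate the WAV-12 about their individual therapy at the same post-allocation visits, including 3 months. In TAU the rater is the psychotherapist or social worker who gives the sessions. State in Data analysis that these visit scores are the ones used in the mediation model.

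Say what the baseline rating refers to, or drop that cell. The 12-month cell can stay. Any per-session ratings in DBT can be kept as a within-arm supplement, outside the comparison of arms.

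The cost is a footnote, form instructions, and a 12-item form for TAU patients and therapists at visits that already exist. Three-month TAU ratings already missed cannot be recovered. The article appeared in March 2020 and predicted recruitment until July 2020, so later participants could still benefit.

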#### Primary outcomes

The primary outcome will be assessed as the total score of the Suicidal Ideation Attributes Scale (SIDAS) plus the Lifetime Parasuicide Count (LPC).

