### Objectives

#### Primary objective

The primary objective of this study is to determine the efficacy of DBT treatment in persons with ASD on suicidal and/or self-harming behaviour.
► *Hypothesis 1*: DBT treatment is effective in decreasing suicidal and/or self-harming behaviour in the persons with ASD as measured by the combined score on Suicidal Ideation Attributes Scale (SIDAS) [30] and Lifetime Parasuicide Count (LPC) [31] in the first 6 months of treatment, compared to treatment as usual (TAU), and that this difference between the groups is sustained at 12 months.

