### Inclusion criteria

Age between 18 and 65 yearsMeets DSM-5 criteria for autism spectrum disorder [45]Suicidal ideation (SIDAS score ≥ 21) [30] and/or level of suicidality/self-harming behaviour rated as severe on the LPC (score = 2 on any item) [31]Outpatient status

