##### Lifetime Parasuicide count (LPC)

The Lifetime Parasuicide Count is a structured, face to face interview for assessing information regarding lethality, intention to die, level of medical treatment received, and specific details of the participant’s first, most recent, and most severe episodes of parasuicide [31]. The LPC measures the level of self-injurious behaviours and suicide attempts. The scores of the SIDAS and LPC will be combined in order to evaluate the multiple aspects of suicidal mood and behaviour.

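### The primary outcome adds an unweighted lifetime parasuicide measure to SIDAS with no stated post-randomisation window, so pre-trial self-harm enters the test of a 6-month effect and the total is hard to interpret

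*Protocol article*

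**What the plan says.** Hypothesis 1 (Primary objective) is that "DBT treatment is effective in decreasing suicidal and/or self-harming behaviour in the persons with ASD as measured by the combined score" of SIDAS and LPC. It concerns the first 6 months, is a comparison with TAU, and expects the difference to persist at 12 months.

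The Primary outcomes section gives the rule: "The primary outcome will be assessed as the total score of the Suicidal Ideation Attributes Scale (SIDAS) plus the Lifetime Parasuicide Count (LPC". The LPC section gives the reason: "The scores of the SIDAS and LPC will be combined in order to evaluate the multiple aspects of suicidal mood and behaviour". Neither states weights, standardisation or which LPC score enters the sum, so the literal reading is a raw sum.

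The LPC section says that the interview collects "specific details of the participant’s first, most recent, and most severe episodes of parasuicide" and also that "The LPC measures the level of self-injurious behaviours and suicide attempts". Table 1 schedules the LPC at screening, baseline, post-treatment and follow-up. The only recall period in the article is the preceding year, and it is mentioned for screening (Recruitment and study procedures). Inclusion criteria show that the LPC also has item ratings: "rated as severe on the LPC (score = 2 on any item".

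The Data analysis section plans a linear mixed model with the baseline value as covariate. It discusses regression to the mean for SIDAS only.

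**The concern.** The hypothesis is about change after treatment starts, but one of the two summed parts is by name and content a lifetime measure. For someone with a history, the first episode is fixed. The worst episode ever can only stay the same or be replaced by a worse one. A lifetime count can only stay the same or rise. Full remission of self-harm would therefore leave these parts where they were at baseline, and any fall in the total would have to come from ideation.

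Adding raw scores creates a second problem: the scale with the larger spread decides what the total mostly measures. A between-arm difference in the total could reflect ideation, new self-harm or altered recall of old episodes, and the total alone would not show which. This matters because it is the only primary endpoint.

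**Working it through.** **1. The plan's own figure.** For effect size 0.50, two-sided alpha 0.05 and power 0.80, the two-sample t-test needs 63.77, so 64 per arm and 128 in total (power 0.801). The stated sample size reproduces and is not at fault.

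**2. What the LPC parts can do in a participant who stops self-harming at randomisation, with no window applied.**
- First episode: unchanged.
- Most severe episode: unchanged.
- Lifetime count: unchanged.
- Most recent episode: still the same pre-trial episode. Its severity could fall only if a later, milder episode replaced it.

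**3. Carrying the screening window forward.** A 12-month look-back at the 6-month visit reaches 12 − 6 = 6 months before randomisation.

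**4. Which component dominates.** The article gives no SDs. Assume SIDAS SD 10, LPC SD s, and no correlation between them. The LPC share of the variance of the sum is s²/(100 + s²): 20% at s = 5, 50% at s = 10 and 80% at s = 20.

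**5. What the baseline covariate leaves.** Further assumptions, none from the article: a 5-point SIDAS effect (5/10 = 0.50, the planned size), SIDAS baseline-to-outcome correlation 0.5, no treatment effect on the LPC, re-report reliability ρ, and new-episode SD a. With the summed baseline as the single covariate:

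- slope = (50 + ρs²)/(100 + s²)
- residual variance V = 100 + s² + a² − (50 + ρs²)²/(100 + s²)
- d = 5/√V, and power = Φ(d√32 − 1.96) with 64 per arm

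SIDAS alone: V = 100 − 50²/100 = 75, d = 0.577, power 0.90.

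Equal SDs (s = 10), ρ = 1: the slope is 150/200 = 0.75. SIDAS needs 0.5 and a carried-forward LPC needs 1.0, so one slope fits neither.
- ρ = 1, a = 0: V = 200 − 150²/200 = 87.5, d = 0.535, power 0.86.
- ρ = 1, a = 2: V = 204 − 150²/200 = 91.5, d = 0.523, power 0.84.
- ρ = 0.9, a = 2: V = 204 − 140²/200 = 106, d = 0.486, power 0.78.

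Adjusted power over a range of LPC SDs:

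| LPC SD | ρ = 1, a = 0 | ρ = 1, a = 2 | ρ = 0.9, a = 2 |
|---|---|---|---|
| 5 | 0.89 | 0.87 | 0.86 |
| 10 | 0.86 | 0.84 | 0.78 |
| 20 | 0.83 | 0.81 | 0.59 |
| 40 | 0.81 | 0.80 | 0.29 |

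The noncentral t gives values up to 0.01 lower.

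**6. Two baseline covariates instead of one.** V = 75 + s²(1 − ρ²) + a². At s = 10 with ρ = 1, a = 2, V = 79 and power is 0.89 (from 0.84). With ρ = 0.9, a = 2, V = 75 + 19 + 4 = 98 and power is about 0.81 (from 0.78).

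**7. Can a count that never falls still separate the arms?** In an illustrative simulation of a purely cumulative count (4,000 runs, 64 per arm, mean history about 20, overdispersed new episodes averaging 3 in one arm and 1.5 in the other), power was 0.88 with the baseline count as covariate and 0.07 without it.

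**The case against.** The strongest reply is that the article is a condensed document, and that recall window and item scoring usually sit in the full protocol, case report form or analysis plan. Silence on those alone is not a defect. What remains is what the article does state: a lifetime instrument, its content, its repetition after randomisation, and an addition rule for the primary endpoint.

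Three stronger readings are tempting, and the article does not support them.

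- **That the LPC score cannot fall at all.** The interview also covers the most recent episode, has item ratings, and is described as a level of behaviour. A score built on those could fall. The limit is established only for lifetime-count and worst-ever parts.
- **That the outcome cannot show the hypothesised effect, or is swamped by noise.** Hypothesis 1 is a comparison with TAU, so fewer new episodes under DBT could separate the arms (step 7). The planned baseline covariate absorbs much of the history. The severe losses in the table need an LPC SD two to four times that of SIDAS together with imperfect recall and no effect on new episodes. Nothing in the article points to such spreads.
- **That SIDAS alone should be primary.** Patients may enter on a severe LPC rating without high SIDAS, and the primary objective names self-harm. Dropping the behavioural part would be a trade-off, not a correction.

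**Conclusion.** The point holds as a defect in how the primary outcome is fixed. Following the text puts pre-randomisation self-harm, and an unscaled sum of two different measures, into the test of a 6-month effect. The worst-ever and lifetime-count parts cannot register remission in a participant, and the meaning of the total depends on which scale has the larger SD.

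The cost in power is real but conditional. At equal SDs it falls from 0.90 for SIDAS alone to about 0.84 to 0.86 with perfect recall, and to 0.78 with re-report reliability 0.9. All SDs, correlations and the absence of an LPC effect are assumptions. The main harm is to interpretation, which does not depend on them.

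**What to change.** 1. At 6 and 12 months, score the LPC only on episodes since the previous assessment. Table 1 has no LPC at 3 months, so each window is about 6 months. Use a matching baseline window where the baseline interviews allow it; otherwise adjust for the baseline LPC as collected.
2. Replace the raw sum with the mean of the two components, each standardised on its pooled baseline SD.
3. Enter baseline SIDAS and baseline LPC as separate covariates.
4. Report each component, with its interval, beside the composite.
5. Declare the amendment before unblinding. Trial status says that data collection is ongoing.

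The cost is one amendment and a dated window in an interview that is already scheduled. There are two downsides. A windowed LPC will be sparser than a lifetime one, and the primary definition changes after registration. The article does not show whether completed baseline interviews dated the episodes, so the matching baseline window may not be recoverable for everyone.
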